### Cost-effectiveness data collection and analysis

As a secondary outcome measure, we will assess the cost-effectiveness of watchful waiting compared to immediate antibiotic prescription, as measured through the incremental cost-effectiveness ratio (ICER). The ICER is defined as:$$ "\mathrm{ICER}"=\left({\mathrm{C}}_{\_2}-{\mathrm{C}}_{\_1}\right)/\left({\mathrm{Q}}_{\_2}-{\mathrm{Q}}_{\_1}\right) $$

where *C*_*i*_ and *Q*_*i*_ denote costs and Quality-adjusted Life Years (QALYs) [40] associated with the treatment received in trial arm *i*, and *i* is 1 for antibiotic treatment and 2 for watchful waiting.

#### Costs of treatment

Costs of treatment including medication costs, health service usage and non-medical costs will be computed for events related to AOM and its treatment. This information will be collected as follows:Medication costs will be calculated using parent/carer-reported antibiotic/analgesia usage collected in the CRFsHealth service usage data will be collected mostly in the CRFs, but also through medical record review. The medical record data will be reviewed within two distinct time periods: 0 to 7 weeks post recruitment and 7 weeks to 3 months post recruitment. Medical record data relating to weeks 0 to 7 will be compared with CRF data to check and enhance reliability of health service usage information. The medical record data from week 7 to 3 months will allow collection of later information, if any, relating to health service utilisation, such as later follow-up appointments relating to the ear disease or its complications. We will estimate costs of health service utilisation and complications by applying publicly available price factors to utilisation figures. Complications requiring a hospital admission will be priced using the National Public Cost Weight Tables [41]. Complications requiring a visit to a medical practitioner will be priced according to item numbers within the Australian universal health benefit scheme, MedicareNon-medical costs will be calculated from parent/carer data collected in the CRF. We will use a societal point of view and, therefore, include non-medical costs, both tangible and intangible, borne by the carers of the child. The main non-medical tangible cost is transportation to and from the GP or any other health care provider. The main non-medical non-tangible cost is time spent by parents/carers in activities related to the AOM or its treatment, which take them away from their usual role or activities. The parent/carer estimate of the time spent on such activities will be converted into a monetary figure using standard guidelines for wages and productivity [42].

#### Quality-adjusted Life Years (QALYs)

We will calculate QALYs using CRF data from parent/carers. The CRF data will be used to measure the time a child spends in different health states associated with both the natural course of the disease (mostly characterised by pain), and complications (such as rash or gastrointestinal problems). Each health state will be assigned a utility value (that measures the degree of preference society places on that health state) using QALY weights found in the medical literature, since a novel evaluation of preferences is not in the scope of this trial. QALYs will then be computed by combining the information about the time spent in the different health states with the QALY weights.

Missing cost-effectiveness data will be managed through the use of imputation, rather than deleting observations. Sensitivity analysis is particularly important, since QALY weights currently available are not specific to the Aboriginal and Torres Strait Islander population. Sensitivity analysis will be performed using both one-way and multi-way Monte Carlo simulations, and will allow us to estimate how much the uncertainty regarding QALY estimates contributes to the overall results. In both cases the key output is the set of conditions under which the ICER remains in an acceptable range, in order for watchful waiting to be considered cost-effective.

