### Sample size and power

With 198 children in each arm of the study, the study will have 80 % power to detect a non-inferiority margin of up to 10 % at a significance level of 5 %, assuming a clinical improvement rate of at least 80 % in both study groups [38]. Allowing for a dropout rate of up to 20 % at days 5 − 10, the total sample size required is 495 children.

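### An acceptable range for the ICER is a poor key output when the QALY difference is plausibly near zero with uncertain sign; net monetary benefit should carry the cost-effectiveness decision

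*Protocol article*

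**What the plan says.** In the protocol article, *Cost-effectiveness data collection and analysis* sets cost-effectiveness as a secondary outcome, "as measured through the incremental cost-effectiveness ratio (ICER"), defined as (C2 − C1)/(Q2 − Q1), where 1 is antibiotic treatment and 2 is watchful waiting.

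*Quality-adjusted Life Years (QALYs)* builds QALYs from carer-reported time in health states (pain, and complications such as rash or gastrointestinal problems) combined with utility weights from the literature. On uncertainty it says: "Sensitivity analysis will be performed using both one-way and multi-way Monte Carlo simulations". It then states the criterion for both kinds of analysis: "the key output is the set of conditions under which the ICER remains in an acceptable range". The purpose given is to judge whether watchful waiting counts as cost-effective. Neither section mentions net benefit, the quadrants of the cost-effectiveness plane, or how the ratio is read when the QALY difference is zero or negative.

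On time horizon, *Costs of treatment* adds record review after the last carer contact: "The medical record data from week 7 to 3 months will allow collection of later information". For the denominator, the QALY section says: "We will calculate QALYs using CRF data from parent/carers".

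**The concern.** A ratio is a usable decision measure only if its denominator is clearly away from zero and of known sign. Three features of this trial point the other way:

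- The sample size is set "assuming a clinical improvement rate of at least 80 % in both study groups".
- *Diagnosis and management of AOM* describes antibiotics as shortening symptoms a little while adding side effects, so the two QALY components pull in opposite directions.
- The health states counted last days, so any QALY difference is a very small number.

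If the QALY difference is near zero, the ICER can be hugely positive or hugely negative by chance, and the same value can describe opposite results. If watchful waiting is cheaper but slightly worse, a result that a non-inferiority design is prepared to accept, the ICER is the saving per QALY given up, and a higher value is the favourable one. At stake is whether the stated output of the economic evaluation can support a conclusion.

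**Working it through.** Write ΔC = C2 − C1, ΔQ = Q2 − Q1, λ for the threshold per QALY, and NMB = λ·ΔQ − ΔC for incremental net monetary benefit.

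**Step 1. The plan's own figure.** Inputs from *Sample size and power*: 80% in both arms, margin 10 points, 80% power, 5% level. With a one-sided 5% level and no true difference:

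n = (1.645 + 0.842)² × (0.8×0.2 + 0.8×0.2)/0.10² = 6.18 × 32 = 197.8, so 198 per arm. Then 396/0.8 = 495.

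Both figures reproduce, so the design assumes no difference in day-7 resolution. That assumption is about resolution, not QALYs.

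**Step 2. Algebra, free of assumed figures.** NMB > 0 means λ·ΔQ > ΔC.
- If ΔQ > 0, this is ICER < λ.
- If ΔQ < 0, dividing by ΔQ reverses the inequality: ICER > λ.

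Changing the sign of both ΔC and ΔQ leaves the ICER unchanged and reverses the sign of NMB. So every ICER value other than λ itself fits one favourable and one unfavourable result. No range on the ratio, however drawn, separates them without the sign of ΔQ.

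**Step 3. Numbers** (λ = 50,000 and the differences are assumed):

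| ΔC | ΔQ | ICER | NMB | Position |
|---|---|---|---|---|
| −20 | +0.0004 | −50,000 | 20 + 20 = +40 | dominant |
| +20 | −0.0004 | −50,000 | −20 − 20 = −40 | dominated |
| −20 | −0.0001 | 200,000 | −5 + 20 = +15 | cheaper, slightly worse |
| −20 | −0.001 | 20,000 | −50 + 20 = −30 | cheaper, worse |

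**Step 4. Instability.** The article gives no costs, utilities or threshold, so all of these are assumptions: utility loss in pain 0.1 to 0.3; SD of symptom days 3; 198 per arm; true ΔC = −20 with SE 10; λ = 50,000. One symptom day is (utility loss)/365.25 = 0.00027 to 0.00082 QALY. The SE of ΔQ is 3 × (utility loss)/365.25 × √(2/198) = 0.000083 to 0.000248. Results from 200,000 draws per scenario, with entries in the order of utility loss 0.1 / 0.2 / 0.3:

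| True effect of watchful waiting | Central 95% of ICER (millions) | P(ICER < 50,000) | P(NMB > 0) |
|---|---|---|---|
| no difference | −3.76 to 3.93 / −1.96 to 1.95 / −1.29 to 1.27 | 0.52 / 0.55 / 0.60 | 0.97 / 0.94 / 0.90 |
| half a symptom day worse | −0.68 to 1.21 / −0.35 to 0.61 / −0.23 to 0.40 | 0.16 / 0.36 / 0.56 | 0.89 / 0.69 / 0.49 |
| one symptom day worse | 0.00 to 0.22 / 0.00 to 0.11 / 0.00 to 0.07 | 0.28 / 0.72 / 0.91 | 0.72 / 0.28 / 0.09 |

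With no true difference, ΔQ is negative in about half the draws. If watchful waiting is half a day better, the two readings nearly agree (about 0.95 against 0.99 or more). The third column reads the range as an upper ceiling, which is an assumption of this check. The second column does not depend on it.

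**Step 5. Horizons.** In Table 1 the symptoms questionnaire and diary end at day 14, the last carer contact is week 7, and only record review takes place at 3 months. *Costs of treatment* counts service use to 3 months. As written, an event between week 7 and 3 months can add cost but no QALY loss.

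**The case against.** The strongest reply is that the article never says the ICER must lie below a ceiling. It speaks of a range, and a range can be defined by quadrant, for instance as a minimum saving per QALY lost when watchful waiting is cheaper and worse. The sentence also concerns the sensitivity analyses, whose stated purpose is uncertainty in the QALY estimates, and need not be the base-case rule. The threshold, the quadrant reading and an acceptability curve are commonly left to a health-economics plan, which is not shown. Finally, equal 80% rates describe day-7 resolution, and fewer side effects could make the QALY difference positive.

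Most of this stands, and it limits what can be claimed. A reader might infer from Step 4 that the trial would reach the wrong economic decision in a large share of cases. The documents do not support that: the ceiling, the costs and the symptom-day scenarios are assumed. In the one-day-worse rows ΔQ lies more than three SEs below zero, so the contrast there comes from the direction of reading, not from instability. A reader might also infer that a negative QALY difference is expected, or that leaving the threshold undefined is an error. Neither follows.

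What the reply does not remove is Step 2. A range becomes workable only once the sign of ΔQ is brought in, and the article fixes the ratio as the measure without doing so.

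**Conclusion.** The point holds as one about a badly suited measure. The article makes the ICER the measure of cost-effectiveness, and its staying in a range the key output of the sensitivity analyses. In this design the QALY difference is plausibly near zero and of uncertain sign. That rests on the equal-resolution assumption and on the described trade-off between symptoms and side effects; it is not a stated figure.

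In that region the ratio is unstable, and one range cannot tell dominant from dominated or read the cheaper-but-worse quadrant correctly. This part is algebra. The size of the instability (about ±1.3 to ±3.9 million per QALY at zero difference) and of any misreading depends on the assumed inputs.

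The difference in horizons is a minor, separate matter. The article itself allows that there may be no later data, and nothing shows that they would move the result.

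The measure should be changed because the change is cheap. The primary non-inferiority conclusion is untouched.

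**What to change.** - Make incremental net monetary benefit (threshold × QALY difference − cost difference), with its 95% CI over a stated range of thresholds, the decision measure and the key output of the planned Monte Carlo analyses.
- Show the joint cost and QALY draws on the cost-effectiveness plane, with an acceptability curve.
- Report the cost difference and the QALY difference separately, each with its interval.
- Keep the ICER, but state its quadrant and direction of reading, and do not use it as the sole criterion. In the cheaper-but-worse quadrant it remains interpretable as saving per QALY given up, so it should not be withheld there.
- Report results with costs cut at week 7, the common horizon, alongside results with costs to 3 months. Choosing week 7 alone would drop the late complication costs that the trial sets out to collect.

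The cost is a wording change in the economic analysis section and slightly more analysis work. No new data are needed, and the planned simulations can be used.

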### Qualitative data collection and analysis

We will undertake a qualitative study using thematic analysis of individual and group interviews to examine parents’/carers’, health professionals’ and researchers’ experiences of the trial and views on the different treatment approaches to AOM. Semi-structured interviews will be undertaken with consenting health care providers (Aboriginal health workers, nurses, GPs, allied health providers) and parent/carers in selected sites, including parent/carers who declined to take part in the RCT. Interview participants will be selected using a purposive sampling strategy for maximal variation of age, gender, study experiences and views [43]. Interviews will also be undertaken with consenting research officers and the community reference groups in each site. The interviews will be taped, transcribed, de-identified and coded. Transcripts will be coded by two members of the research team with contrasting disciplinary perspectives, and any differences in interpretation resolved by discussion, and a thematic analysis undertaken [44].

## Discussion

The WATCH trial will answer the important clinical question: whether watchful waiting is (or is not) inferior to immediate antibiotic therapy for urban Aboriginal children with AOM who are at low risk of complications. We will assess the cost-effectiveness of the two approaches and qualitatively examine the acceptability of the alternate approaches to management of AOM to parents and carers, and health care providers. Furthermore, we will examine experiences of the trial process itself in order to inform future RCT studies in Aboriginal health settings.

This trial will make an important contribution to the evidence base for the safe management of AOM in urban Aboriginal children. Australian guidelines for the management of AOM have recently been updated [5] and Aboriginal and Torres Strait Islander children living in urban settings are no longer classified as high risk for complications of AOM, and thus health care providers are advised they should be treated with watchful waiting. This requires a change in clinical practice. The expert consensus guideline advice has been extrapolated from studies in low-risk, developed countries internationally. There have been no studies into the relative effectiveness of a watchful waiting approach for urban Aboriginal and Torres Strait Islander children, nor of attitudes of carers and health care providers to this approach.

Research undertaken with Aboriginal and Torres Strait Islander people must have net benefits for communities, incorporate community research control, be conducted in a manner sensitive to the cultural principles of Aboriginal society, be appropriately resourced and enhance the skills and knowledge of the Aboriginal and Torres Strait Islander people, communities and organisations that are participating in the project [34]. This study has been designed with awareness and commitment to these guiding principles and to the flexibility required to undertake a randomised controlled trial in Aboriginal and Torres Strait Islander health settings.

Ear health is a core priority for Aboriginal communities and the health care providers who work with those communities. Aboriginal and Torres Strait Islander people experience marked disadvantage compared to other Australians [45] and effective treatment of ear disease and prevention of hearing impairment in Aboriginal children is vital to maximise health and learning outcomes [22]. The ultimate goal of this research is to ensure appropriate treatment of acute infections of the middle ear so as to maintain the ear health of Aboriginal children and decrease their risk of developing chronic complications.

### Trial status

The trial is registered with the Australia New Zealand Clinical Trials Registry (ACTRN12613001068752). Contracts have been signed with six participating health services, which were selected based on service size and geographic location. Four ACCHSs declined to participate in the trial when approached for potential participation. Training and orientation to the study has been undertaken in all sites and recruitment has commenced in five sites. There was a protocol change made after one child was recruited to the study. This comprised:Revision of the diagnostic criteria of AOM to comprise ‘ear pain *or irritability*’ in a child aged 2 to 3 years)Amendment to the primary outcome to allow the GP to assess the outcome (resolution of AOM) through assessment of parental report and review of VO- and RO-collected temperature if the child had not come in to see the GPRemoval of a requirement for tympanometry and VO at the day-3 and day-14 data collection points, allowing data to be collected by telephone rather than face-to-face

Another protocol change to eligibility inclusion criteria was made after 36 children were recruited to the study, permitting the eligibility diagnosis of AOM without perforation and the day-7 primary outcome assessment by the treating nurse practitioner as well as the GP. This was deemed necessary as it was the normal practice in one of the later recruiting sites for diagnosis and treatment of AOM to be determined by credentialed nurse practitioners at the health service.

## Abbreviations

ACCHS: Aboriginal Community Controlled Health Services
AI: associate investigator
AMS: Aboriginal Medical Service
ANOVA: analysis of variance
AOM: acute otitis media
CRF: case report form
CSOM: chronic suppurative otitis media
GP: general practitioner
ICER: incremental cost-effectiveness ratio
NP: nurse practitioner
OM: otitis media
QALYs: Quality-adjusted life Years
RCT: randomised controlled trial
RO: research officer
VO: video-pneumatic otoscopy
WATCH: Watchful waiting for Aboriginal and Torres Strait Islander Children with acute otitis media: the WATCH trial
